## Abstract

**Background::**

Acute graft-vs-host disease (aGVHD) is a common complication of allogenic hematopoietic stem-cell transplantation (allo-HSCT) and skin is the most common and often the 1st site at which aGVHD develops. Cutaneous aGVHD is usually treated with oral and/or topical corticosteroids as the 1st-line treatment; however, steroid-refractory aGVHD not only impairs patients’ quality of life but also causes significant morbidity and mortality after allo-HSCT. Narrow-band ultraviolet B (NB-UVB) phototherapy has been utilized for a wide range of immunologic inflammatory skin diseases, but there is limited information on the efficacy, safety, and biomarkers for response prediction of NB-UVB for cutaneous aGVHD.

**Aims::**

The purpose of this study is to investigate the efficacy and safety of NB-UVB phototherapy for steroid-refractory cutaneous aGVHD.

**Patients and methods::**

A total of 40 subjects aged from 16 to 70 years with steroid-refractory cutaneous aGVHD after allo-HSCT will be included in the trial. Patients with worse than stage 2 intestine/liver aGVHD will be excluded. Eligible patients will undergo NB-UVB phototherapy until resolution or further worsening of rash or occurrence of an unmanageable adverse event. The primary endpoint is the overall response rate. The secondary outcomes include rates for complete response, partial response, stable disease, progressive disease, duration of response, sparing effect on calcineurin inhibitors and/or corticosteroids, safety, and predictive biomarkers for treatment response.

**Ethics and dissemination::**

The protocol has been approved by the institutional Clinical Research Review Board of Kyoto Prefectural University of Medicine. Written informed consent will be obtained from all patients before registration, in accordance with the Declaration of Helsinki. Results of the study will be disseminated via publications in peer-reviewed journals.

**Trial registration::**

Trial registration numbers UMIN000032426 and jRCTs052180005.

## Introduction

1

Allogenic hematopoietic stem-cell transplantation (allo-HSCT) is one of the best curative options for various malignant and nonmalignant hematologic disorders those are otherwise lethal. This is because this strategy includes not only the combined effects of intensive preparative cytotoxic treatment but also a potent graft-vs-tumor (GVT) effect through an allogeneic immune reaction with hematopoietic recovery by transfer of allogenic hematopoietic cells. However, transplanted immune cells also potentially cause immunologic attacks against normal tissues of recipients, and such so-called graft-vs-host disease (GVHD) may sometimes be severe.

Acute graft-vs-host disease (aGVHD), which normally affects the skin, liver, or gastrointestinal tract, accounts for 30% to 70% of major adverse events following allo-HSCT, despite prophylaxis with immunosuppressive agents.^[1]^ Corticosteroids are the frontline therapy for aGVHD, with response rates of approximately 40%.^[2]^ However, there is no promising salvage treatment for steroid-refractory (SR) aGVHD. Various systemic immunosuppressive interventions, such as use of antithymocyte globulin (ATG), immunosuppressive biologic agents, and mesenchymal stromal cells, have been used to treat SR-aGVHD, but their efficacies have not been satisfactory. Moreover, there is major concern regarding the excessive systemic immunosuppression induced by these therapies, which potentially increases the risk of infectious complications, disease recurrence, and emergence of secondary malignancy.^[1,3–7]^ In addition, ATG, biologic agents, and MSCs have high associated medical costs. Given this situation, SR-aGVHD is an important cause of morbidity and mortality as well as an economical issue after allo-HSCT.^[8,9]^ Thus, there is a high unmet medical need for establishment of effective and safe treatment for SR-aGVHD.

Skin is the most common and often the 1st site at which aGVHD develops, and the condition can be present as a single affected site or with multiple organ involvement. In general, cutaneous aGVHD initially manifests as a papular eruption that can be both focal and systemic, but when uncontrolled, it expands systemically and leads to desquamation resembling toxic epidermal necrosis. Thus, according to clinical stage and overall grading of aGVHD based on the affected skin area and the degree of other organ involvement, direct topical corticosteroids are commonly utilized for isolated grade I, stages 1 to 2 cutaneous aGVHD; while systemic corticosteroids are used as 1st-line salvage therapy for worse aGVHD of grades II to IV. However, even in a case with isolated cutaneous aGVHD without other organ involvement, more intensive systemic immunosuppressive therapy is still commonly used for SR-aGVHD. Recently, successful disease control of cutaneous aGVHD by ultraviolet-based phototherapy has been repeatedly reported in patients with skin involvement as the predominant feature of SR-aGVHD.^[10–13]^

Narrow-band ultraviolet B (NB-UVB) has a peak wavelength of 311 to 312 nm and excludes the shorter, photobiologically more erythrogenic wavelengths in UVB. Thus, it has been widely used as an effective and safe phototherapy for inflammatory skin diseases such as psoriasis, atopic dermatitis, and vitiligo vulgaris. With the assumption that the immunosuppressive effects of NB-UVB can be directed to skin, NB-UVB phototherapy is likely to impair systemic immune function.^[14]^ However, to date, NB-UVB phototherapy has not been approved for cutaneous aGVHD in Japan. Previous clinical studies of NB-UVB phototherapy for cutaneous aGVHD have included limited numbers of participants.^[10,11]^ Furthermore, although it is purported that NB-UVB therapy has fewer side effects and a lower long-term carcinogenic effect than those of psoralen plus ultraviolet,^[15]^ these properties have not been substantiated in patients treated by allo-HSCT. Therefore, we plan to investigate the efficacy and safety of NB-UVB phototherapy for cutaneous SR-aGVHD prospectively in the present study.

## Methods

2

### Study design

2.1

An open-label, single-center, nonrandomized, single-arm phase 2 intervention study will be conducted to examine the efficacy and safety of NB-UVB therapy for cutaneous SR-aGVHD. The protocol has been reviewed and approved by the institutional Clinical Research Review Board of Kyoto Prefectural University Hospital. Written informed consent will be obtained from patients before registration by research physicians in accordance with the Declaration of Helsinki. At least annual independent monitoring will be planned in accordance with Japanese clinical trial guidelines.

### Endpoints

2.2

#### Primary endpoint

2.2.1

The primary endpoint is the overall response rate (ORR), which is defined as the proportion of patients with a partial response (PR) or a complete response (CR).

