### Participants

2.3

The inclusion criteria are patients diagnosed with cutaneous SR-aGVHD, where “steroid-refractory” is defined as progression or no improvement after 5 consecutive days of topical or oral corticosteroids, or recurrence during tapering off of oral steroids; histologically confirmed cutaneous aGVHD (patients who do not undergo skin biopsy will only be included if the lesion is clearly diagnosed by the clinical course); and grades I to II aGVHD (stage 1, 2, or 3 cutaneous aGVHD and less than stage 1 intestinal/liver aGVHD); who are of age ≥16 to <70 years at the time of enrollment; have a performance status of 0 to 2 defined by Eastern Cooperative Oncology Group Criteria; provide written informed consent to participate in the study; are an outpatient or inpatient; and are of any gender.

The exclusion criteria are patients who are pregnant, nursing, or possibly pregnant; or have poorly controlled diabetes mellitus, uncontrolled infection, difficult-to-treat skin disease other than aGVHD, grade III or worse aGVHD, photosensitivity, or are judged to be inappropriate for the study by an attending physician.

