### Data collection

2.5

We will collect the following information in screening prior to the 1st NB-UVB irradiation: age, sex, diagnosis of hematologic disease and disease status, clinical aGVHD stage and grade, physical examination data, standard laboratory test results, and efficacy of concomitant aGVHD medication. Treatment visits, which will include a physical examination, clinical aGVHD grading, standard laboratory tests, evaluation of concomitant medication for aGVHD, and assessment of adverse events, will be performed at least weekly. aGVHD will be graded according to consensus criteria.^[16]^ CR is defined as the complete resolution of rash, PR as a decrease in cutaneous aGVHD stage of at least 1 level, and PD as worsening of the skin aGVHD stage. NC indicates nonresponders. Adverse events will be evaluated using National Cancer Institute Common Toxicity Criteria (CTCAE) ver. 4.0. In addition, protocol-specified immunophenotypic analysis will be performed to calculate the absolute numbers of peripheral blood immune cells (i.e., B cells, T cells, NK cells, CD4/CD8-positive T cells, and regulatory T cells) and serum cytokine analysis for IL-1, IL-8, and IL-17 at 3 points: within 7 days prior to the 1st NB-UVB irradiation, at 2 months from the start of NB-UVB, and at the end of the treatment.

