### Rationale for the setting of the number of enrolled participants

2.6

All participants enrolled in the study (full analysis set, FAS); that is, subjects excluding patients with serious violations (such as a serious protocol deviation and violation of inclusion/exclusion criteria) or revocation of consent from the FAS (per protocol set); and those among the FAS in which protocol treatment is provided at least once (safety analysis set) will be analyzed. By assuming that the threshold response rate is 50% and the expected response rate is 75% at a one-sided significance level α = 5% and a power of 1 − *β* = 80%, it is calculated that 25 patients are required for the 1st stage in Simon 2-stage theory.^[17]^ Assuming a dropout rate of 30% due to organ damage, complications after allo-HSCT, or relapse of underlying disease, and a 10% rate of inappropriate enrollments, we therefore set the target number of patients as 40.

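### The primary ORR counts a fall in skin stage as an NB-UVB response even when systemic aGVHD treatment was started or increased during the course

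*Protocol article*

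**What the plan says.** Section 2.2.1 of the protocol article makes ORR the primary endpoint, "which is defined as the proportion of patients with a partial response (PR) or a complete response (CR"). Section 2.5 supplies the components: "CR is defined as the complete resolution of rash, PR as a decrease in cutaneous aGVHD stage of at least 1 level". Neither section attaches a condition on other aGVHD treatment.

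Other treatment is nevertheless expected and recorded. In Section 2.5 the treatment visits include "evaluation of concomitant medication for aGVHD, and assessment of adverse events, will be performed at least weekly". The only analysis described for these data is the secondary sparing endpoint in Section 2.7, which counts dose reductions. Increases enter no endpoint.

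Section 2.3 defines steroid-refractory as "progression or no improvement after 5 consecutive days of topical or oral corticosteroids, or recurrence during tapering off of oral steroids". A patient can therefore enter without having failed a systemic steroid, or while flaring on a falling oral dose. The Introduction adds that intensified systemic immunosuppression remains common in refractory disease, even when only the skin is involved.

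Section 2.6 sets the benchmark: "By assuming that the threshold response rate is 50% and the expected response rate is 75" per cent, "at a one-sided significance level α = 5% and a power of 1 − *β* = 80" per cent.

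**The concern.** A single-arm trial has no control group to absorb the effect of other treatment. Whatever meets the response definition is compared with 50% and read as the effect of NB-UVB. If a patient's systemic steroid is started or raised during the course and the rash then falls by one stage, the definition records a PR, and nothing in the analysis separates that patient from one who improved on NB-UVB alone.

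The effect runs in one direction, since added treatment can turn a non-response into a response under this rule but not the reverse. It also bears on the purpose of the trial. The Discussion presents NB-UVB as an option for patients who might otherwise need intensive systemic treatment, and a response obtained with more systemic treatment does not support that.

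**Working it through.** **1. The plan's own figure.** Section 2.6 says "it is calculated that 25 patients are required for the 1st stage in Simon 2-stage theory". Exact enumeration of Simon designs for 50% versus 75%, one-sided 5%, power 80%, gives this optimal design: continue if more than 6 of the first 11 respond, and declare success if more than 16 of 25 respond. At 50% it passes with probability 0.0458, and at 75% with probability 0.8005. So 25 reproduces, as the total of that design (its first stage is 11). The target of 40 also reproduces: 25/(0.7 × 0.9) = 39.7, rounded up. The article states no decision rule, so this one is inferred from the match with 25.

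**2. Inputs for the check.**
- True ORR attributable to NB-UVB: 0.50, the threshold in Section 2.6.
- f, the share of NB-UVB non-responders whose systemic aGVHD treatment is started or increased during the course and before they are classified: not in the documents. Assumed 10% to 30%.
- q, the share of those patients whose skin stage then falls: not in the documents for this population. The Introduction says "Corticosteroids are the frontline therapy for aGVHD, with response rates of approximately 40" per cent, but that is a frontline rate and these patients are refractory to at least topical steroid. Assumed range 20% to 40%, with the quoted figure as the upper end.

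**3. Formulas.**

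Apparent ORR: p = 0.50 + 0.50 × f × q.

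Pass probability: the sum over x = 7 to 11 of P(X1 = x) × P(X2 ≥ 17 − x), with X1 ~ Bin(11, p) and X2 ~ Bin(14, p).

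**4. Results.** For example, f = 0.30 and q = 0.40 give p = 0.50 + 0.50 × 0.12 = 0.56.

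| f | q | Apparent ORR | Pass probability |
|---|---|---|---|
| 0 | – | 50% | 4.6% |
| 10% | 20% | 51% | 5.6% |
| 10% | 40% | 52% | 6.8% |
| 20% | 20% | 52% | 6.8% |
| 20% | 40% | 54% | 9.8% |
| 30% | 20% | 53% | 8.2% |
| 30% | 40% | 56% | 13.6% |

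**5. Dependence on the inferred rule.** The same inputs were put through single-stage rules, with p running from 50% (no added treatment) through 51% to 56%.

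| Rule | p = 50% | p = 51% | p = 56% |
|---|---|---|---|
| At least 16 of 23 | 4.7% | 5.7% | 13.5% |
| At least 26 of 40 | 4.0% | 5.3% | 16.2% |
| At least 18 of 25 | 2.2% | 2.7% | 7.7% |

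Under every rule the pass probability rises. Under the last, which starts well below 5%, several of the scenarios stay below 5%: at p = 53% it is 4.2%.

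**The case against.** The strongest reply is that this is silence in a condensed article. No sentence permits systemic treatment to be started or escalated during NB-UVB, and the full protocol may restrict it. That stands as a limit: the point concerns the published definition, and the documents do not show that escalation will occur often. It does not remove the point, because the article fixes a response rule that has no such condition, and its entry criteria make added treatment likely enough to need one.

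A reader might infer something stronger: that skin clearing under systemic treatment given after NB-UVB has stopped also counts. The text points the other way. Section 2.4 stops NB-UVB at PD, NC, or new or worse gut or liver aGVHD. Section 2.5 places grading at treatment visits and names NC patients as non-responders. Section 2.7 dates duration of response from a documented response to NB-UVB. The natural reading is assessment during the course, although the article does not say so outright.

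The same sections undercut the larger scenarios. With q = 40%, the formula gives a pass probability of 24.0% if half of the non-responders receive added treatment and 62.0% if all do. Those figures would require that many patients to be escalated before being classified as PD or NC and taken off treatment. The documents do not support that.

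Three further cautions stand. The 40% is a frontline steroid rate. The decision rule is inferred. No source is given for the 50% threshold, so it may already reflect patients on background systemic drugs, in which case the comparison would be partly like with like. Counting added treatment as non-response is also one legitimate choice among others, and too broad a version would misclassify true responders whose dose rose for an unrelated reason.

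**Conclusion.** The concern holds in a limited form. The response definition depends on skin stage alone. A response that follows systemic aGVHD treatment started or increased during the course is therefore credited to NB-UVB, and in this design that can only raise the ORR.

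The direction is clear from the text, but the size is not. The range of about 5.6% to 13.6%, against 4.6%, rests on the assumed f and q, on the inferred Simon rule, and on a 50% threshold that does not already include such responses. It illustrates what could happen and does not estimate the trial's actual error rate. The matter should be settled in the definition, since medication is already reviewed at least weekly and the article reports only 2 subjects enrolled as of April 2019.

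**What to change.** In Sections 2.2.1 and 2.5, add:

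- For the primary ORR, a patient counts as a non-responder if, before a response is documented, a new systemic treatment for aGVHD is started or systemic immunosuppression is increased because of aGVHD. Dose changes for other reasons, such as prophylaxis, do not count.
- Response is assessed during the NB-UVB course.
- ORR regardless of added treatment is reported as a sensitivity analysis.

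This changes how patients are counted, not how they are treated. The cost is a few sentences, plus recording the reason for each increase alongside the medication review already planned. The reported primary ORR may be lower. If the full protocol already contains such a rule, the article needs only to state it.

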#### Secondary endpoints

2.2.2

The secondary endpoints are rates for CR, PR, stable disease (SD), and progressive disease (PD), duration of response (DoR), sparing effect on calcineurin inhibitors and/or corticosteroids, adverse events, profile of peripheral blood immune cells, including B cells, T cells, NK cells, CD4/CD8-positive T cells, and regulatory T cells, in association with the response to NB-UVB, and peripheral blood levels of inflammatory cytokines, such as interleukin (IL)-1, IL-8, and IL-17, in association with the response to NB-UVB.

### Participants

2.3

The inclusion criteria are patients diagnosed with cutaneous SR-aGVHD, where “steroid-refractory” is defined as progression or no improvement after 5 consecutive days of topical or oral corticosteroids, or recurrence during tapering off of oral steroids; histologically confirmed cutaneous aGVHD (patients who do not undergo skin biopsy will only be included if the lesion is clearly diagnosed by the clinical course); and grades I to II aGVHD (stage 1, 2, or 3 cutaneous aGVHD and less than stage 1 intestinal/liver aGVHD); who are of age ≥16 to <70 years at the time of enrollment; have a performance status of 0 to 2 defined by Eastern Cooperative Oncology Group Criteria; provide written informed consent to participate in the study; are an outpatient or inpatient; and are of any gender.

The exclusion criteria are patients who are pregnant, nursing, or possibly pregnant; or have poorly controlled diabetes mellitus, uncontrolled infection, difficult-to-treat skin disease other than aGVHD, grade III or worse aGVHD, photosensitivity, or are judged to be inappropriate for the study by an attending physician.

### NB-UVB phototherapy protocol

2.4

The NB-UVB phototherapy will be administered using a UV7001K-TL01 system (Waldmann-Lichttechnik, Villingen-Schwenningen, Germany) with peak emission at 311 to 313 nm (narrow band). Irradiation will be performed thrice a week in general; however, the frequency can be reduced to once or twice a week based on the severity of cutaneous aGVHD. Before irradiation, the minimal erythema dose (MED) will be determined by exposing different areas of each patient's upper back to a range of NB-UVB doses to identify the lowest dose that produces erythema within 24 hours. Initial NB-UVB will be started at 70% of MED and increased in steps of 20% up to 4-times MED or 120 times. In a case with development of slight erythema, treatment will be continued at the same dosage. In a case with erythema with pain or bulla formation, treatment will be withheld until erythema or bulla resolves and the dose will be reduced by 50% in resumed treatment. NB-UVB will be discontinued if the patient achieves CR, PD, NC, or continuous PR without further improvement. In a case with emergence of intestinal/liver aGVHD or worsening of coexisting intestinal/liver aGVHD during NB-UVB, the study treatment will also be discontinued.

### Data collection

2.5

We will collect the following information in screening prior to the 1st NB-UVB irradiation: age, sex, diagnosis of hematologic disease and disease status, clinical aGVHD stage and grade, physical examination data, standard laboratory test results, and efficacy of concomitant aGVHD medication. Treatment visits, which will include a physical examination, clinical aGVHD grading, standard laboratory tests, evaluation of concomitant medication for aGVHD, and assessment of adverse events, will be performed at least weekly. aGVHD will be graded according to consensus criteria.^[16]^ CR is defined as the complete resolution of rash, PR as a decrease in cutaneous aGVHD stage of at least 1 level, and PD as worsening of the skin aGVHD stage. NC indicates nonresponders. Adverse events will be evaluated using National Cancer Institute Common Toxicity Criteria (CTCAE) ver. 4.0. In addition, protocol-specified immunophenotypic analysis will be performed to calculate the absolute numbers of peripheral blood immune cells (i.e., B cells, T cells, NK cells, CD4/CD8-positive T cells, and regulatory T cells) and serum cytokine analysis for IL-1, IL-8, and IL-17 at 3 points: within 7 days prior to the 1st NB-UVB irradiation, at 2 months from the start of NB-UVB, and at the end of the treatment.

### Rationale for the setting of the number of enrolled participants

2.6

All participants enrolled in the study (full analysis set, FAS); that is, subjects excluding patients with serious violations (such as a serious protocol deviation and violation of inclusion/exclusion criteria) or revocation of consent from the FAS (per protocol set); and those among the FAS in which protocol treatment is provided at least once (safety analysis set) will be analyzed. By assuming that the threshold response rate is 50% and the expected response rate is 75% at a one-sided significance level α = 5% and a power of 1 − *β* = 80%, it is calculated that 25 patients are required for the 1st stage in Simon 2-stage theory.^[17]^ Assuming a dropout rate of 30% due to organ damage, complications after allo-HSCT, or relapse of underlying disease, and a 10% rate of inappropriate enrollments, we therefore set the target number of patients as 40.

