### Statistical analysis

2.7

1.ORR: a cumulative rate of CR rate and PR rate.2.DoR: Time from documentation of response to NB-UVB to re-worsening of cutaneous aGVHD.3.Sparing effect on calcineurin inhibitors and/or corticosteroids: Rate of patients in which the dose of calcineurin inhibitors and/or corticosteroids can be reduced after the initiation of NB-UVB.

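### The 25 patients described as Simon's first stage are the total of Simon's optimal design for the stated inputs; its first stage is 11

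*Protocol article*

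**What the plan says.** Section 2.6 of the protocol article (rationale for the number of participants) fixes four inputs: a threshold response rate of 50%, an expected rate of 75%, a one-sided significance level of 5% and power of 80%. From these it concludes that "it is calculated that 25 patients are required for the 1st stage in Simon 2-stage theory".

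It then allows for losses. The first allowance is "Assuming a dropout rate of 30% due to organ damage, complications after allo-HSCT, or relapse of underlying disease", and the second is 10% for inappropriate enrolments. The result is "we therefore set the target number of patients as 40".

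The section gives no second-stage size. Section 2.7 describes the primary outcome only as "ORR: a cumulative rate of CR rate and PR rate".

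**The concern.** In a Simon two-stage design the first stage is the smaller group after which the trial may stop for lack of activity, and the total is what the final test uses. Section 2.6 gives one number, assigns it to the first stage, and builds the whole enrolment target on it. If the label is right, the second stage has no patients. If 25 is the whole evaluable sample, the label is wrong. The two statements cannot both stand.

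A team that takes the sentence literally would reach its first decision only when accrual is complete. It would forgo the futility stop for which the Simon design is chosen, and would test the primary endpoint in 25 patients with error rates other than those stated.

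**Working it through.** **Inputs, all from section 2.6.** p0 = 0.50, p1 = 0.75, one-sided alpha ≤ 0.05, power ≥ 0.80; stated first stage 25; losses 30% and 10%; target 40.

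**1. Reproducing the 25.** A two-stage design enrols n1 patients, stops if r1 or fewer respond, otherwise continues to n, and is positive if more than r respond. The probability of a positive result at response rate p is

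Σ over x from r1+1 to n1 of P(X1 = x) × P(X2 ≥ r + 1 − x),

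with X1 ~ Bin(n1, p) and X2 ~ Bin(n − n1, p). Searching all combinations that meet the alpha and power limits gives:

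| Design | Stage 1 | Total | Alpha | Power |
|---|---|---|---|---|
| Optimal (smallest expected size at p0) | 11, stop if ≤6 respond | 25, positive if ≥17 | 0.0458 | 0.8005 |
| Minimax (smallest total) | 14, stop if ≤7 respond | 23, positive if ≥16 | 0.0462 | 0.8016 |

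The figure 25 is reproduced exactly as the optimal design's total. It is not the first stage of either standard design.

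**2. Reproducing the 40.** Applying the two loss rates in turn: 25/(0.7 × 0.9) = 25/0.63 = 39.7, rounded up to 40. In reverse, 40 × 0.63 = 25.2 evaluable patients. (Adding the rates instead gives 25/0.6 = 41.7, or 42.) The target therefore provides the 25 and nothing for a further stage.

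**3. What a single look at 25 delivers.** With X ~ Bin(25, p):

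| Positive if | Alpha, P at p = 0.50 | Power, P at p = 0.75 |
|---|---|---|
| ≥16/25 | 0.115 | 0.929 |
| ≥17/25 | 0.0539 | 0.851 |
| ≥18/25 | 0.0216 | 0.727 |

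Moving from 17 to 18 takes alpha from above 5% to well below it, and power from above 80% to below it. No cut-off at n = 25 meets both targets. The optimal design meets them with the same 25 patients because its early stop removes some false positives, bringing alpha from 5.4% to 4.6%.

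**4. What the early look is worth.** P(X1 ≤ 6 | n1 = 11, p = 0.5) = 1486/2048 = 0.726. Expected evaluable size under the null is 11 + (1 − 0.726) × 14 = 14.8, against 25 without the look.

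**5. Can 25 be a first stage at all?** Yes. Designs with n1 = 25 that meet both limits exist for totals of 26 and above. One example: stop if ≤13/25, otherwise continue to 40, positive if ≥26/40 (alpha 0.040, power 0.944). They are neither optimal nor minimax, and all need evaluable patients beyond 25, which the derivation in step 2 does not supply.

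**The case against.** The strongest reply is that this is one wrong word. The inputs return 25 exactly as the optimal total, and 25 with the stated losses returns 40 exactly. That is what one would see if the calculation had been done correctly as 11 then 25 and mislabelled in writing. On that reading the sample size is right, the targets are met (alpha 4.6%, power 80.1%), and nothing in the conduct of the trial changes. This stands as a possibility, and the article cannot exclude it.

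A second reply is that the article condenses a fuller protocol, and that stage sizes and stopping boundaries are commonly left there. This also stands. The silence of sections 2.6 and 2.7 on boundaries is not counted as an error here, and the outcome definition in section 2.7 contradicts nothing.

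A third is that the single-look figures assume a test that the article does not specify, in exactly 25 patients, whereas section 2.6 also names a full analysis set of everyone enrolled. This is fair, and those figures are offered only as the consequence of a first look at 25 evaluable patients.

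None of this rescues the sentence itself. It states that the stated inputs require 25 patients in the first stage, and they do not.

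Two stronger readings are tempting and should be resisted. A reader might infer that the trial has no futility look and is therefore underpowered or over-liberal; the article shows only that its description is wrong. A reader might also infer that a first stage of 25 is impossible; step 5 of the working shows otherwise.

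**Conclusion.** The stated first-stage size is wrong for the stated inputs, and the enrolment target built on it makes the paragraph inconsistent with itself. That much is exact and needs no assumption beyond the inputs in section 2.6 and the standard optimal or minimax criterion.

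The consequence depends on what the full protocol does:

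- **If the trial follows the article literally**, with its first look at 25 evaluable patients, one of the two targets is missed. Alpha is 5.4% with power 85.1%, or alpha is 2.2% with power 72.7%. The 73% chance of stopping an ineffective treatment at 11 patients is also lost.
- **If the full protocol runs 6/11 then 16/25**, both targets are met and the defect is the label alone.

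Because the error concerns the size and decision basis of the primary endpoint, and the literal reading changes both, it should be corrected and not left to interpretation.

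**What to change.** Check the full protocol first, then replace the sentence in section 2.6 according to what it shows.

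**If an interim look is planned or still possible:** state that 25 is the total evaluable number and give the design. Suggested text: *Simon optimal two-stage design: 11 patients in stage 1; stop if 6 or fewer respond; otherwise continue to 25 in total; the treatment is considered active if 17 or more of 25 respond (exact alpha 4.6%, power 80.1%).* The minimax design (7/14, then 15/23) is an equally valid choice.

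**If no interim look is or can be made:** drop the Simon reference and state an exact single-stage rule with its true operating characteristics. Examples are at least 18 of 25 (alpha 2.2%, power 72.7%) and at least 16 of 23 (alpha 4.7%, power 80.4%). The rule should be fixed before responses are tabulated.

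The cost is one paragraph and, for the two-stage version, one count of responders after 11 evaluable patients. The target of 40 need not change. Section 2.9 reports 2 subjects enrolled by April 2019, so the look was still ahead at that date; whether it still is cannot be told from the article.
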